# Study protocol for a parallel-group, double-blinded, randomized, controlled, noninferiority trial: the effect and safety of hybrid electroconvulsive therapy (Hybrid-ECT) compared with routine electroconvulsive therapy in patients with depression

**DOI:** 10.1186/s12888-019-2320-3

**Published:** 2019-11-06

**Keywords:** Study protocol, Randomized controlled trial, Hybrid electroconvulsive therapy, Electroconvulsive therapy, Depression

## Abstract

**Background:**

Electroconvulsive therapy (ECT) is the most rapid and effective treatment for patients with depression, ECT can achieve remarkable antidepressant effects in the initial 3–4 sessions, but significant side effects limit its use. However, recent low-charge electrotherapy (LCE) studies have demonstrated antidepressant or antipsychotic effects with significantly fewer side effects. The aim of this study is to propose a novel two-step charge set strategy for ECT treatment, referred to as Hybrid-ECT, to decrease side effects by using a low charge while preserving treatment efficacy.

**Methods/design:**

A randomized, double-blinded, standard-controlled, parallel-group design will be carried out. We plan to enroll 112 inpatients diagnosed with depression (unipolar or bipolar) and randomly assign them to conventional ECT (control group) or to Hybrid-ECT (treatment group, 3 ECT sessions followed by LCE sessions (approximately 2.8 joules per session)). We will evaluate participants across a wide variety of domains including clinical symptoms, cognitive, psychological and functional metrics. We will also perform magnetic resonance imaging (MRI) and event-related potential (ERPs) assessments during treatment to explore brain function differences between ECT and LCE.

**Discussion:**

This research proposes a simple but completely novel ECT strategy that aims to rapidly relieve depressive symptoms and minimize side effects. The mechanism of ECT and LCE will be further discussed.

**Trial registration:**

Chinese Clinical Trial Registry, Number: ChiCTR1900022905 (Registration date: April 30, 2019).

## Background

Globally, major depressive disorder (MDD) is one of the most common psychiatric disorders, rated as one of the five leading cause of years lived with disability (YLDs) in 2016 and associated with substantial disabilities [1]. Patients with depression often show high suicide risk [2], severe impairments in social function [3] and cognitive dysfunction [4]. According to the 1995–1999 mortality data provided by the Minister of Health of the People’s Republic of China, the mean annual suicide rate was 23 per 100 000, and there were a total of 287 000 suicide deaths per year [5]. Therefore, it is especially important to quickly and effectively treat depression patients.

Electroconvulsive therapy (ECT) administered with anesthesia and neuromuscular blockers is the most effective treatment for depression [6–9]. However, the use of ECT is impeded by adverse effects (AEs), such as acute headache, dizziness and confusion [10], especially the cognitive function impairments, which may be affected by the stimulus intensity, number of treatments or electrode placement [11, 12]. Thus, researchers have been working on methods to quickly relieve symptoms while minimizing side effects.

One important feature of ECT is the rapid antidepressant effect in the early stage of treatment. Kellner et al. conducted a double-blind, controlled trial to compare the efficacy and cognitive effects of three electrode placement methods in ECT [13]. The results demonstrated that all placements resulted in rapid remission over the early course of treatment; during the first 3–4 ECT sessions, the bitemporal placement resulted in a more rapid decrease in symptom ratings than the other placements, followed by small changes in symptom ratings in the subsequent sessions for all placement groups. Some articles have reported that patients could go into remission after the first ECT session [14–16]. The findings indicated that the decline in symptom rating of later stage was not as rapid as the early period; furthermore, as the number of ECT sessions increased, the side effects became more pronounced [17], which suggests that we should change the mode of ECT procedure.

At present, based on existing ECT knowledge, a charge-induced seizure is considered to be a key feature. However, after reviewing the literature, we found an interesting phenomenon. Some ECTs that failed to induce seizures also demonstrated antidepressant effects but without severe side effects [18–20]. The safety and efficacy of low-charge nonconvulsive electrotherapy (NET) for MDD was first studied in detail by Regenold et al. in 2015 [21]. The authors demonstrated that the therapeutic effect of NET in patients with resistant MDD was similar to that of ECT, while serious AEs were not observed. Although the study was small, unblinded, nonrandomized and uncontrolled by a sham or standard procedure, and the results were susceptible to both investigator and subject bias, they exhibited the potential of low-charge electrotherapy (LCE) for mental diseases and raised the following question: are high charges or seizures essential? Subsequently, a double-blind, randomized, controlled pilot clinical trial with schizophrenia patients was conducted by our team; the results suggested that LCE (2.8 joules per session) without seizures exerted similar antipsychotic effects while causing fewer AEs than ECT [22]. Although the sample sizes have been small, LCE has the potential to be a safe and effective treatment for patients with schizophrenia or depression. However, our inhouse data (detailed information please see Additional file 3: Table S2 and Additional file 4: Figure S1) revealed that LCE relieved depression more slowly in the first few sessions than ECT.

Considering that patients with depression need quick symptom relief with few side effects, we propose a new two-step charge set strategy for ECT treatment, referred to as Hybrid-ECT. In Hybrid-ECT, conventional ECT is conducted during the first 3 sessions (the first step) because according to Kellner’s research, the Hamilton Rating Scale for Depression (HAMD-24) score reduction trajectory is steep during the first 3 ECT sessions (an approximation based on Figure 2 of Kellner’s article [13]), and then LCE is conducted until the treatment is terminated (the second step). We hope that the two-step Hybrid-ECT could combine ECT’s strength of an early rapid antidepressant effect and LCE’s advantage of fewer side effects. Therefore, our hypotheses were as follows: 1) Hybrid-ECT exerts a noninferior antidepressant effect relative to ECT over the whole course of the treatment; and 2) compared with the routine ECT charge set strategy, Hybrid-ECT may cause fewer AEs, especially in the later part of treatment (i.e., after 3 ECT sessions). To test these hypotheses, we designed the present randomized, double-blinded, parallel-group, controlled clinical trial. Since the intervention arm of this trial is a change in the current ECT charge setting strategy, routine ECT was selected as the standard-control group; and the trial is designed as a noninferiority study on the antidepressant effects of Hybrid-ECT and ECT.

## Methods/design

### Study design

This clinical trial is a randomized, double-blinded, parallel-group, standard-controlled, noninferiority study to detect the efficacy and side effects of a novel ECT charge setting strategy called Hybrid-ECT for the treatment of patients with depression compared to routine ECT. Participants, neuropsychological measurement raters, magnetic resonance imaging (MRI) and event-related potential (ERP) operators, patient psychiatrists, nurses, and researchers will be blinded to the patient treatment assignment. After each ECT/LCE procedure, the ECT operator will reset the energy parameters to prevent others from detecting the participant’s group. The study flow chart is shown in Fig. 1.

**Fig. 1 Fig1:**
[figure not shown]
Study flow chart

### Study population and recruitment

A total of 112 inpatients with unipolar or bipolar depression will be recruited by psychiatrists in Shenzhen Kangning Hospital (Mental Health Center of Shenzhen city, which has more than 1000 beds) in Shenzhen city, Guangdong Province, PR China.

### Inclusion criteria

Patient (18 < age < 60) accepted ECT for treatment because of severe depression and on a stable psychotropic medication regime more than 2 weeks;Patient met the following ICD-10 criteria [23] for diagnosis of unipolar or bipolar depression (F31.4, F31.5, F32, F33);Patient had an HAMD-24 score > 21;Patient was competent to provide informed consent; and.Patient was sufficiently fluent in Chinese to ensure valid responses to the neuropsychological tests.

### Exclusion criteria

Failure to respond to earlier ECT;ECT within the last 6 months;Rapid-cycling or mixed-episode bipolar disorder;Medication use incompatible with ECT treatment (such as lithium, benzodiazepine, antiepileptic drugs, etc.). Use of these drugs will be stopped at least 5 half-lives before the start of treatment;Inability to follow the study protocol;Unstable, serious comorbid medical condition (Parkinson’s disease, multiple sclerosis, stroke, alcohol use disorder, etc.) or history of epilepsy;Intelligence quotient (IQ) ≤ 70 tested by the Wechsler Adult Intelligence Scale 4th edition [24];≤ 9 years of education;Pregnancy or women without adequate contraception; and.Young Mania Rating Scale (YMRS) score [25] > 20.

### Withdrawal criteria

The patient will be withdrawn and unblinded at any time if the exclusion criteria are met, the psychiatrist finds that the patient could be better served with other treatments, there is a decrease in the HAMD-24 score of < 3 points between the latest two visits, or the patient decides to withdraw. When a patient withdraws his or her consent, the reason and withdrawal date will be recorded.

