##### Stimulus

The energy set of the first three sessions is the same as that in the ECT group; the subsequent sessions use LCE, and the energy is set to the minimum (2.8 J) with a stimulus duration = 0.5 s and a frequency = 20 Hz, as we have previously reported [22].

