##### Randomization

After receiving detailed information about this trial, signing the consent form, passing the eligibility screen and completing the baseline test, the enrolled patients will be assigned a sequential patient number. If a patient discontinues from the study between the randomization and the first ECT procedure, the patient will be excluded from the final analyses, and he or she will not be allowed to rejoin the study.

A statistician with no other connection to the trial will generate the randomization sequence using the default random number generator of SAS version 9.4 (SAS Institute Inc., Cary, NC, USA). The randomization sequence list will remain concealed from the investigators. A research nurse who will not participate in the clinical evaluation will assign the participants to their group.

Participants, neuropsychological measurement raters, MRI and ERP operators, patient psychiatrists, nurses, and researchers will be blinded to the patient treatment assignment. If unblinding is determined to be necessary, the investigators must report all unblinding (with reason) on the corresponding case report form (CRF).

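### Every withdrawal triggers unblinding automatically, with no check that anyone needs the allocation

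*Protocol article*

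**What the plan says.** Only the protocol article is at hand.

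- **Withdrawal criteria.** "The patient will be withdrawn and unblinded at any time if the exclusion criteria are met". The list continues with "the psychiatrist finds that the patient could be better served with other treatments", then a HAMD-24 decrease of less than 3 points between the two most recent visits, and ends with "or the patient decides to withdraw". The section does not say who learns the allocation, or whether ratings stop at withdrawal.
- **Randomization.** "Participants, neuropsychological measurement raters, MRI and ERP operators, patient psychiatrists, nurses, and researchers will be blinded to the patient treatment assignment". The next sentence reads "If unblinding is determined to be necessary, the investigators must report all unblinding (with reason" and names the case report form as the place to report it.
- **Study design.** After each session "the ECT operator will reset the energy parameters to prevent others from detecting" a participant's group.
- **Hybrid-ECT group, Stimulus.** The first three sessions match the control arm; "the subsequent sessions use LCE, and the energy is set to the minimum (2.8 J", that is, low-charge electrotherapy (LCE).
- **Study population and recruitment.** All patients come from one site and "will be recruited by psychiatrists in Shenzhen Kangning Hospital".
- **Primary outcome measure.** Change in total HAMD-24 from baseline to visit t5.

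**The concern.** Breaking the blind is normally a separate decision from stopping treatment, made when someone needs the allocation to care for the patient. Here the two are joined in one verb phrase, so disclosure follows even when it serves no purpose.

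What is at stake is the blinding that the Study design and Randomization sections set up. HAMD-24 is scored by a rater, the site is a single hospital, and one withdrawal trigger is the judgement of a psychiatrist who is meant to be blinded. If treating staff routinely learn the allocation of departing patients, they may begin to connect visible features of a treatment course with one arm and guess better for later patients.

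The rule may also apply fairly often. The Background says that the trial of three electrode placements saw fast early improvement and then only small changes in later sessions. A patient who improves and then levels off could meet the 3-point trigger.

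**Working it through.** The point contains no figure to recompute, and the sample size of 112 does not depend on it. The check is a comparison of the text.

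**Step 1. What the rule attaches to each trigger (Withdrawal criteria).**

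| Trigger | Unblinding attached | Need tested | Could the allocation help further care? |
|---|---|---|---|
| Exclusion criterion met | yes | no | not stated; would depend on the criterion |
| Psychiatrist prefers other treatment | yes | no | plausibly, once the arms differ |
| HAMD-24 fall of less than 3 points | yes | no | plausibly, once the arms differ |
| Patient's own decision | yes | no | sometimes, if more treatment follows; no reason given |

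Unblinding is attached to 4 of 4 triggers and a test of need to 0 of 4.

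**Step 2. Timing.** The rule applies at any time. Both arms receive the same ECT in sessions 1 to 3 and diverge only from session 4. For a withdrawal before session 4, whatever the trigger, the allocation tells a clinician nothing about the treatment already received. It shows only what was planned next.

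**Step 3. Withdrawal criteria against Randomization.** Randomization opens its sentence with a condition of necessity and then requires that all unblinding be reported with a reason. It does not say that unblinding may occur *only* when necessary. The two sections can therefore both be obeyed: unblind at withdrawal, then report it. What the withdrawal rule leaves no room for is the judgement of need that the Randomization wording presupposes.

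**Step 4. Could disclosure come before data that count?**
- The Withdrawal criteria do not say that ratings end at withdrawal. The MRI protocol places the t5 scan about 7 days after the last session. If withdrawn patients are still asked to attend t5 (an assumption, since Table 1 is not shown), a rating could follow disclosure.
- The Statistical analyses section keeps every patient with one treatment and one later measurement, so data from withdrawn patients can enter the main analysis.
- The blinding assessment asks participants and raters to guess the allocation at each visit after randomization. A guess from someone already told says nothing about blinding.

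**Step 5. Size.** The document gives no withdrawal rate by trigger, no visit spacing, no list of who is told and no schedule after withdrawal. No bias in HAMD-24 points can be calculated.

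**The case against.** The strongest reply is that nothing conflicts. The Withdrawal criteria can be read as fixing in advance when unblinding occurs, and Randomization as saying how it is reported. This stands. A reader might infer a flat contradiction, or that the protocol blinds every listed role without exception, but the text does not support either. The Randomization sentence is a reporting duty that covers all unblinding, and it directly follows the list of blinded roles.

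Second, no route to bias is demonstrated. If assessment ends at withdrawal, disclosure comes after that patient's last rating. The sequence is concealed and no block structure is stated, so nothing shows that one patient's allocation reveals another's. This also stands. A reader might infer that raters are told and that the primary comparison is biased, but the document says neither. A possible exposure remains, because the text does not stop ratings at withdrawal.

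Third, a patient who leaves by choice entered with severe depression and may need more treatment, so the next clinician may have good reason to ask whether recent sessions were ECT or LCE. This is fair. It would be wrong to say that a voluntary exit never creates a need. It supports deciding case by case, which the present wording does not allow.

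Fourth, operational detail on who is told usually sits in the full protocol. That is true, and its absence is not criticised here. The point concerns a rule that the article states outright.

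**Conclusion.** The point holds in a limited form. The Withdrawal criteria make unblinding automatic for all four triggers, including voluntary exit and the 3-point HAMD-24 rule, without any judgement of need. This sits poorly with the Randomization wording but does not contradict it. It is an avoidable and unquantified risk to blinding in a single-hospital trial with a rater-scored primary outcome.

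The conclusion rests on the plain grammatical reading that one verb phrase governs the whole list. That the risk reaches HAMD-24 data further assumes either that ratings can follow withdrawal or that disclosed allocations help staff guess for other patients. The document neither confirms nor excludes these. Severity is minor: a cheap improvement.

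**What to change.** In the Withdrawal criteria, delete the words *and unblinded* and add, for example:

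*Whatever the reason for withdrawal, the allocation is disclosed only when the patient's further care needs it (for instance, when the next treatment depends on whether recent sessions were ECT or LCE), and only to the clinician who needs it. The reason is recorded on the case report form as set out under Randomization. Raters stay blind for any HAMD-24 rating made after withdrawal.*

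The cost is amended wording in one section, with no added visits, procedures or patients. The downside is that the treating clinician must request the allocation instead of receiving it by default. Unblinding that care requires stays available for every trigger.

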### Outcome measures

#### Visit procedure

Patients will be interviewed during twelve visits. The detailed visit procedure is shown in Table 1.

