#### Primary outcome measure

The primary outcome measure is the change in total HAMD-24 score at endpoint (visit t_5_) from baseline.

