#### MRI protocol

MRI will be performed at 3 time points: t_0_ (~ 24–48 h before baseline), t_1_ (~ 24–48 h after the three first ECT and before the fourth ECT/LCE) and t_5_ (~ 7 days the last of ECT/LCE). All participants will be scanned at the Shenzhen Kangning Hospital Neuropsychiatry Imaging Center in a 3 T Discovery MR750 scanner (GE Healthcare, Milwaukee, USA) equipped with an eight-channel head coil. A standard MRI protocol will be applied at each time point, including a T1-weighted spoiled gradient echo, SPGR (TE = min full; TR = 6.7 ms; flip angle = 12°; field of view =256 mm; voxel size = 1.0 * 1.0 * 1.0 mm^3^; matrix = 256 * 256); a T2-weighted high resolution hippocampus sequence (TE = 50 ms; TR = 8020.0 ms; flip angle = 122°; field of view =175 mm; voxel size = 0.4 * 0.4 * 2.0 mm^3^; matrix = 448 * 448); a resting-state fMRI scan with a BOLD sequence (TE = 25 ms; TR = 2000 ms; field of view =220 mm; voxel size = 3.4 * 3.4 * 3.2 mm^3^; matrix = 64 * 64; volume number = 240); a DTI sequence (TE = 81.4 ms; TR = 8724.0 ms; field of view = 224 mm; voxel size = 2.0 * 2.0 * 2.0 mm^3^; matrix = 112 * 112; number of diffusion directions = 64; b values = 0, 1000 s/mm^2^); ^1^H- magnetic resonance spectroscopy (MRS) sequences for the ROIs including the hippocampus, thalamus, anterior cingulate and posterior cingulate (TE = 35.0 ms; TR = 1500 ms) [44–46]; and a 3D ASL sequence (TE = 10.5 ms; TR = 4389 ms; post-labeling delay = 1025 ms; field of view =240 mm).

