## Discussion

### Summary

To the best of our knowledge, this is a completely novel energy set strategy for ECT procedures. We speculate that Hybrid-ECT may rapidly relieve depressive symptoms during the early stage, then we will convert to LCE until the symptoms are completely relieved, and the side effects will occur less often than those in the control group (routine ECT). Furthermore, we will also perform the MRI and ERP assessments before and after the ECT treatment to test the hypothesis that Hybrid-ECT and routine ECT share the same antidepressant mechanisms. The strengths of the study include an innovative experimental design, time-intensive visits, detailed neuropsychological assessments, and MRI and ERP examinations to accurately document the differences in efficacy and side effects between Hybrid-ECT and ECT.

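### The HAMD-24 withdrawal rule does not exempt responders or remitters, so it also withdraws and unblinds successes whose score has levelled off

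*Protocol article*

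**What the plan says.** All references are to the Protocol article.

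- **Withdrawal criteria.** The consequence and timing are set by "The patient will be withdrawn and unblinded at any time if the exclusion criteria are met". The list that follows includes a second trigger: "there is a decrease in the HAMD-24 score of < 3 points between the latest two visits". Nothing in it refers to the level of the score or to total improvement.
- **Secondary outcome measures.** Response is a reduction of more than 50% from baseline, and remission is HAMD-24 below 10, both assessed at t5. They are defined only as outcomes and are not linked to withdrawal or to stopping treatment.
- **Primary outcome measure.** "The primary outcome measure is the change in total HAMD-24 score at endpoint", which is visit t5.
- **Background.** In the cited trial of electrode placements, the rapid early fall was "followed by small changes in symptom ratings in the subsequent sessions for all placement groups".
- **Discussion, Summary.** The intended course in the Hybrid-ECT arm is "then we will convert to LCE until the symptoms are completely relieved". Complete relief is not defined.
- **MRI protocol.** Visit t5 is placed at about "7 days the last of ECT/LCE", so it is tied to the end of treatment.
- **Visit procedure.** "Patients will be interviewed during twelve visits". The table showing which visits include HAMD-24 is not available here.

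**The concern.** The rule looks intended to stop patients who are not improving. As worded, it tests only the latest step in the score, and a small step has two opposite causes: the patient has not improved, or the patient has improved and levelled off. The design rationale itself expects a steep early fall and then a flatter course, so the second cause is foreseeable.

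A success caught by the rule is recorded as a withdrawal and unblinded. If t5 is not collected afterwards, the primary mixed model loses some precision, and the chi-square or Fisher comparisons of response and remission at t5 lose patients whose success was already documented. If t5 is collected, the rating follows an unblinding in a trial that relies on blinded raters. The Randomization section, by contrast, treats unblinding as something done only when judged necessary.

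**Working it through.** **1. The plan's own figure.** Inputs from Sample size and power calculation: margin 4.0, SD 8.0, one-sided alpha 0.05, power 0.8, drop-out 10%.

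n per arm = 2 × (1.645 + 0.842)² × 8² / 4² = 49.5, rounded up to 50. Then 50 / 0.9 = 55.6, rounded up to 56 per arm, or 112 in total. This matches the plan, so the design allows for 10% loss from all causes.

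**2. The rule applied to successes (no assumptions needed).**

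- 32 → 12 → 12: reduction 20/32 = 62.5%, a responder. Last fall 0, so withdrawn.
- 30 → 11 → 9: reduction 21/30 = 70% and score below 10, a responder and remitter. Last fall 2, so withdrawn.
- 6 → 6: a remitter. Last fall 0, so withdrawn.

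Each passing rating needs a fall of at least 3, so a patient at score s can pass at most floor(s/3) more ratings: none at 0–2, one at 3–5, two at 6–8, three at 9.

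**3. Chance of a trigger at one rating.** The document gives no within-patient SD, so 1.5 and 3 points are assumed. Scores are whole numbers, so a fall below 3 means a fall of 2 or less. With true fall d between visits,

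P(trigger) = Φ((2.5 − d) / (SD × √2)).

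| True fall d | SD 1.5 | SD 3 |
|---|---|---|
| 0 (level) | 0.88 | 0.72 |
| 1 | 0.76 | 0.64 |
| 2 | 0.59 | 0.55 |

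**4. Share of patients affected (illustration only).** The HAMD-24 schedule is not shown, so several were tried. Assumptions: about 300,000 simulated patients per setting, baseline mean 32 (SD 5, above 21), patient slope factor SD 0.35, within-patient SD 1.5 and 3. The resulting SD of change is 7.9 to 8.9, in line with the planned 8.0. Three mean paths from t0 to t5 were assumed:

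- A (early plateau): 32, 20, 17, 14, 12, 11
- B: 32, 22, 18, 14, 11, 9
- C (steady fall): 32, 27, 22, 17, 12, 7

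The table gives patients withdrawn before t5 while in response or remission, as a share of all patients, letting those below 10 go straight to t5.

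| HAMD-24 rated at | A | B | C |
|---|---|---|---|
| t1, t2, t3, t4 | 22–23% | 15–17% | 3–7% |
| t1, t2, t4 | 10–14% | 2–8% | 0–1% |
| t1, t3 | 1–4% | 0–1% | 0% |
| t1, t4 | 0–2% | 0–1% | 0% |
| t1 only | 0% | 0% | 0% |

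The last row is exact: a fall below 3 from a baseline above 21 cannot be response or remission. If remitters stay on the schedule and t1–t4 are all rated, the shares are A 40%, B 28–33%, C 5–11%.

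**5. What lost t5 data would cost.** With m evaluable patients per arm, power = Φ(4 / (8 × √(2/m)) − 1.645). Total loss of 10% (m = 50.4) gives 0.81, 20% (m = 44.8) gives 0.77, and 40% (m = 33.6) gives 0.66. The 20% and 40% losses are assumed. The calculation ignores the earlier ratings that the mixed model uses, so it overstates the cost.

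**The case against.** The strongest reply is that the effect rests on a table we cannot see. The illustration includes zero, and with two on-treatment ratings it is at most 4%. The larger shares need an early plateau and dense ratings, and every simulation input is assumed. This stands: no number of affected patients can be claimed.

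Second, fully recovered patients may finish treatment and go to t5 without another rating, so the floor(s/3) count may describe few real patients. This stands in part. Complete relief is undefined and not equated with HAMD-24 below 10, and a responder at 12 has not reached it. The point therefore mainly concerns plateaued responders who continue treatment.

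Third, the cited flattening is per session and for groups, while the rule compares visits that may span several sessions, so small changes can add up to 3 points. That is fair. It makes the trigger less likely but does not exempt anyone.

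Fourth, loss of t5 is not stated. Because t5 is tied to the last session, a stopped patient could still be rated, and a condensed article may leave that detail to the full protocol. This stands, and the harm from missing data is conditional on it. The unblinding, however, is stated outright.

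Fifth, the trigger acts on recorded scores, which the mixed model uses, and a tipping-point analysis is planned. This protects the primary result well, and no bias toward noninferiority is claimed. No similar check is named for the binary rates.

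Finally, successes are only 7–32% of all triggers in the simulation (t1–t4 rated, remitters going to t5). An exemption leaves most triggers in place, as it should if the rule is meant for non-improvers.

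**Conclusion.** The concern holds. The rule is stated in operative terms and, followed literally, withdraws and unblinds patients who have succeeded by the trial's own definitions. That conclusion needs only the text and arithmetic. The per-rating trigger probability for a responder on a level course, 72–88%, rests on the assumed within-patient SD of 1.5 to 3. The share of patients affected may be negligible or substantial (0–23% with remitters going straight to t5, up to 40% otherwise), depending on the unseen rating schedule and on how scores fall. The consequence is limited: some precision in the primary analysis and missing or unblinded success status at t5, with no demonstrated bias toward noninferiority. It should be fixed, because the wording is wrong whatever the count.

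**What to change.** 1. Limit the trigger to patients who do not currently meet the response or remission definition in Secondary outcome measures. Make it a stop of study treatment rather than withdrawal from the study, and unblind only when necessary, in line with the Randomization section.
2. Continue blinded HAMD-24 ratings at the scheduled visits through t5 for everyone who stops study treatment. Use these values in the primary mixed model and in the t5 response and remission rates.
3. Check that the 10% drop-out allowance is consistent with the revised rule.

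The cost is a wording amendment to Withdrawal criteria, plus HAMD-24 ratings at visits already scheduled for patients who stop treatment. Unless the check in item 3 shows otherwise, the sample size need not change.
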